### Study design

2.1

This clinical trial is designed as a randomized, controlled study with the assessors blinded to the treatment allocation. It will be conducted in six medical facilities throughout China, including the Jiangsu Province Hospital with Integration of Chinese and Western Medicine, Huai’an Hospital of Traditional Chinese Medicine, Yancheng Hospital of Traditional Chinese Medicine, Jiangyin Hospital of Traditional Chinese Medicine, Dongtai Hospital of Chinese Medicine, and Nanjing Lishui District Hospital of Traditional Chinese Medicine. The recruitment of participants will occur simultaneously in outpatient settings and hospital wards.

The Institutional Ethics Committee at the coordinating centre has reviewed and granted approval for this study, as indicated by the approval number 2024-LWKYZ-008, which remains valid until February 23, 2027. Prior to participation, all individuals will provide written informed consent. Participants who are enrolled will receive complimentary warm acupuncture treatment. The methodology in this trial is meticulously organized, ensuring that ethical standards are met. The protocol aligns with the Standard Protocol Items: Recommendations for Interventional Trials (SPIRIT) guidelines to uphold scientific integrity (35). Additionally, the results will be reported in accordance with the relevant Consolidated Standards of Reporting Trials (CONSORT) extension guidelines, ensuring rigorous quality control throughout the research (36).

Participants who meet the criteria will be randomly divided into two groups, with an equal ratio of 1:1, assigning them to either the warm acupuncture group or the standard care group. All individuals will participate in a treatment phase lasting 12 weeks, followed by a follow-up period of 1 year. Medical statisticians will analyse the outcome data. This trial has been officially registered with the Chinese Clinical Trial Registry (Registration number: ChiCTR2400082506). The flow of this study is illustrated in Figure 1, while a comprehensive schedule for enrolment, interventions, and assessments is provided in Table 1.

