### Sample size calculation

2.4

This study employs a randomized controlled trial methodology to assess the effectiveness of warm acupuncture for alleviating peripheral neuropathy caused by oxaliplatin, comparing a warm acupuncture cohort with a standard care cohort. The main measure of interest is the neurotoxicity level, which will be evaluated using the NCI-CTCAE version 4.0 criteria. Based on previous research, a treatment response is indicated by a decrease of one or more grades in neurotoxicity (37). The expected response rates for the two groups are 0.8 and 0.47, respectively. Utilizing a standard formula for the comparison of two proportions, with a two-tailed alpha level of 0.05 and a power of 80% (*β* = 0.2), a minimum of 33 participants is necessary for each group. Considering an estimated dropout rate of approximately 20%, the target sample size is established at no less than 40 participants per group. Consequently, the overall sample size for this investigation is set at 84 participants, with 42 in each group.

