Additional statistical details are predefined. In the primary models, we will adjust for key baseline covariates that display an imbalance (*p* < 0.1) or possess established prognostic significance (e.g., number of chemotherapy cycles). If a significant group-by-time interaction is identified, Bonferroni-corrected *post hoc* pairwise comparisons will be conducted. Missing data, assumed to be missing at random, will be managed using the likelihood-based estimation inherent to linear mixed models; the robustness of findings will be assessed through sensitivity analyses, including the last observation carried forward method. All adverse events will be summarized using descriptive statistics, and between-group differences in incidence rates will be evaluated using the Chi-square test or Fisher’s exact test, as appropriate. For participants who withdraw from the study, the primary efficacy analysis will follow the Intention-to-Treat (ITT) principle, with linear mixed models handling missing data under the Missing at Random assumption. A Per-Protocol (PP) analysis will be conducted as a sensitivity measure. All withdrawals and protocol deviations will be recorded with detailed reasons.

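### The plan fixes Bonferroni for the comparisons after a significant interaction; Holm gives the same family-wise 5% control with no extra assumption and never less power

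*Protocol article*

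**What the plan says.** Statistical methods (4.2) of the protocol article plans a GEE or mixed-effects ordinal logistic model of neurotoxicity grade with group, time and their interaction. It then sets the rule for the follow-up comparisons: once the interaction between group and time is significant, "Bonferroni-corrected *post hoc* pairwise comparisons will be conducted". The article does not list which pairs belong to the family.

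Sample size calculation (2.4) rests on one comparison of two proportions at two-sided 0.05 and 80% power. It states that "The expected response rates for the two groups are 0.8 and 0.47, respectively", that "a minimum of 33 participants is necessary for each group", and, after an allowance of about 20% for dropout, that "the overall sample size for this investigation is set at 84 participants, with 42 in each group". No power is claimed for any comparison at a single visit.

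Table 1 schedules the grade at baseline and at weeks 2, 4, 8, 12, 16, 24, 36 and 60, which is eight visits after baseline. The Outcomes section (3.3) lists seven.

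**The concern.** The comparisons after the interaction test show at which visits the arms differ. The Discussion says that the trial is meant to show both immediate and long-term effects. The sections on the outcome, the sample size and the analysis name no single primary time point, so statements about when the treatment works would rest on these comparisons.

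With 33 to 42 patients per arm, dividing alpha by the number of visits is expensive. If another procedure gives the same error control with no extra assumption and at least as much power, part of that cost is avoidable. At stake is how many visits can be declared significant once an interaction is found. The test of the primary model and the sample size are not affected.

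**Working it through.** **1. The plan's own figure.** Inputs from Sample size calculation: p1 = 0.80, p2 = 0.47, difference 0.33, mean 0.635, two-sided alpha 0.05, power 80%. Pooled formula without continuity correction:

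n = [1.960 × √(2 × 0.635 × 0.365) + 0.842 × √(0.80 × 0.20 + 0.47 × 0.53)]² / 0.33² = [1.960 × 0.681 + 0.842 × 0.640]² / 0.1089 = 32.2, so 33 per group.

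Dropout: 33 / 0.8 = 41.25, so 42 per group. Both figures are reproduced.

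**2. Power per visit under Bonferroni.** Assumed family: the between-arm contrasts at the eight visits after baseline, so each is tested at 0.05/8 = 0.00625 (critical value 2.734).

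Power = Φ[(0.33 × √n − 2.734 × 0.681) / 0.640]

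| n per arm | One test at 0.05 | Bonferroni over 8 |
|---|---|---|
| 33 | 81% | 52% |
| 34 | 82% | 54% |
| 42 | 90% | 67% |

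With the seven visits of the Outcomes section, alpha per test is 0.05/7 = 0.00714. Power is then about 54% (n = 33) and 68% (n = 42), so the visit count matters little.

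**3. What Holm changes.** The p-values are ordered and compared in turn with 0.05/8, 0.05/7, 0.05/6, and so on up to 0.05, stopping at the first failure. No threshold is below 0.05/8, so every Bonferroni rejection is kept. The first threshold is the same as Bonferroni's, so the chance of at least one rejection is identical. Holm gains only when several visits show an effect.

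**4. Gain before the interaction test is considered.** The correlation between visits and the pattern of effect are assumptions, because the document gives neither. The simulation used eight equally correlated contrasts, with correlation from 0 to 0.9. The gain is the average power per visit that has an effect, Holm minus Bonferroni.

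| Pattern of the 0.80 vs 0.47 effect | Gain in points |
|---|---|
| Full at all eight visits, normal approximation | 7 to 14 |
| Full at all eight, binary response, 34 per arm | 11 to 13 |
| Full at all eight, binary response, 42 per arm | 12 to 16 |
| Full at six of eight | 5 to 8 |
| Full at four of eight | 3 to 5 |
| Full at two of eight | about 1 |
| Full at one of eight | about 0 |
| Ramped | 3 to 7 |
| Half the effect at all eight | 1.5 to 4 |

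The 16 arises with 42 evaluable per arm and zero correlation between visits, which is implausible for repeated measurements on the same patient.

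**5. Gain through the interaction test.** The comparisons are made only if the interaction is significant, so this condition has to be included.

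- Full effect at all eight visits, baseline not a level of time: the difference between arms is constant, so the interaction is null. The test is passed in only 4 to 5% of runs, and the gain is under 1 point.
- The same pattern with baseline as a level of time: the step from no difference at baseline is itself an interaction. The gain is about 8 to 10 points (normal approximation, correlation 0.4 to 0.8, 33 or 42 per arm).
- Effect at weeks 8 to 24 only: the test is passed in 92 to 99% of runs, and the gain is 2 to 5 points.
- Partial and ramped patterns overall: about 1 to 7 points.

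**The case against.** Bonferroni is prespecified, valid and conservative, and it comes with simple matching simultaneous confidence intervals, which Holm lacks. The comparisons are follow-up tests, and nothing in the passage is misstated or contradicted. All of this stands, and it is why the point is one of efficiency and not of error.

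The power figures come from a two-proportion test on response, whereas the plan analyses the ordinal grade in a longitudinal model. This also stands. They show the order of magnitude and are not the power of the planned analysis.

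Two stronger readings are tempting, and the document supports neither.

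- A reader might infer that Bonferroni simply costs 11 to 14 points per visit. That figure needs the full 0.33 difference at every visit from week 2 to week 60. The article gives one pair of rates with no time point and nowhere assumes such a pattern. It also leaves out the interaction test, which that pattern seldom passes unless baseline is a level of time.
- A reader might infer that the correction runs over every pair of arm-by-visit cells: 2 × 9 = 18 cells, 18 × 17 / 2 = 153 pairs. The article proposes no such family. Between-arm contrasts by visit are the natural reading of a plan that stresses differences between groups, and the list of contrasts may properly stand in the full protocol or the SAP.

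What the objection does not remove is that the article names the procedure, and an SAP that follows it would carry Bonferroni forward.

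**Conclusion.** The point holds as a low-severity improvement. On the same contrasts, Holm gives the same 5% family-wise control under any dependence and never has less power. For eight between-arm contrasts and the planning rates, Bonferroni leaves about 52% (33 per arm) to 67% (42 per arm) power per visit.

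Holm adds roughly 1 to 7 points when the effect is partial, ramped or limited to some visits, and next to nothing if only one visit has an effect. About 8 to 14 points is reached only with the full effect at every visit and the interaction test passed, with baseline as a level of time. The upper part of that range treats the test as always passed. The chance of finding at least one significant visit is the same under both procedures.

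These sizes depend on the assumed effect pattern, the correlation between visits and the family of eight.

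**What to change.** Replace the sentence on post hoc comparisons in Statistical methods (4.2) with:

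> If the group-by-time interaction is significant, between-arm contrasts at the post-baseline visits will be tested with the Holm procedure at family-wise two-sided 0.05; within-arm and cross-visit comparisons are descriptive.

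Report unadjusted or Bonferroni confidence intervals beside the Holm p-values and label them as such, because Holm has no simple matching simultaneous intervals. A Bonferroni interval may then include no difference at a visit that Holm declares significant, and the report should say so.

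Reconcile the eight post-baseline visits of Table 1 with the seven of the Outcomes section (3.3), so that the size of the family is fixed.

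The cost is one sentence, agreed before unblinding. No additional patients, visits or data are needed.

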## Background

1

Oxaliplatin is a platinum-based chemotherapy drug from the third generation that is commonly used to treat different types of solid tumors (1). FOLFOX chemotherapy, which pairs 5-fluorouracil with oxaliplatin, along with the XELOX chemotherapy, which combines capecitabine and oxaliplatin, are recognized as primary standard treatment options for colorectal cancer (2). The main adverse effects of oxaliplatin include peripheral neuropathy, myelosuppression, and gastrointestinal reactions (3).

Oxaliplatin-induced chronic peripheral neuropathy (OICPN) is a significant dose-limiting side effect that can hinder some patients’ ability to adhere to their treatment plans, often leading to reduced dosages or the complete cessation of chemotherapy, which in turn diminishes its effectiveness in clinical settings (4, 5).

Chronic peripheral neuropathy resulting from oxaliplatin affects approximately 40% of individuals undergoing treatment (6). This condition typically manifests as bilateral numbness and pain in a glove-and-stocking pattern, along with slight difficulties in fine motor skills and sensory ataxia. It follows a cumulative, dose-dependent trajectory, generally emerging and intensifying after approximately 3 months of ongoing therapy. Neuropathy classified as Grade 3 is observed in 50% of patients who have received a total dose of 1,170 mg/m^2^ (7). This condition often persists and may worsen even after treatment has ended, a phenomenon known as coasting (8). Research indicates that nearly 60% of patients report ongoing neuropathic symptoms following their last chemotherapy session, with 19% experiencing severe symptoms 18 months later (9). Additionally, 31% of patients continue to endure OICPN 5 years after completing chemotherapy (10). These symptoms significantly diminish the quality of life of cancer survivors.

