### Inclusion criteria

2.2

Participants who met all of the following requirements were considered for inclusion: (1) Aged 18–85 years; (2) Completion of chemotherapy (at least 3 months prior) using the mFOLFOX6 or XELOX regimen*; (3) Presence of chemotherapy-induced peripheral neuropathy with a neurotoxicity grade ≥2 according to the NCI-CTCAE version 4.0; (4) Absence of severe cardiac, hepatic, renal, or hematopoietic system impairments; (5) Karnofsky Performance Status (KPS) score ≥60 and an expected survival of ≥6 months; (6) Absence of any cognitive or mental health issues; possesses typical verbal skills to effectively articulate symptoms and the overall state; (7) Provision of written informed consent.

$$\begin{array}{l} {}*\text{mFOLFOX}6—\text{oxaliplatin},\text{leucovorin},\text{fluorouracil};\\ \text{XELOX}—\text{oxaliplatin},\text{capecitabine} \end{array}$$

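### The one named missing-data sensitivity analysis, last observation carried forward, assumes grades stay fixed after dropout, which the protocol's own expectations contradict

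*Protocol article*

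**What the plan says.** On missing data, Statistical methods (4.2) states: "Missing data, assumed to be missing at random, will be managed using the likelihood-based estimation inherent to linear mixed models". It continues that robustness will be checked by "sensitivity analyses, including the last observation carried forward method". The section presents these details as fixed in advance. The only other analysis labelled as sensitivity is the per-protocol one: "A Per-Protocol (PP) analysis will be conducted as a sensitivity measure".

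Other sections bear on whether grades stay still after a participant leaves:

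- Sample size calculation (2.4) defines response as a fall of at least one grade and states: "The expected response rates for the two groups are 0.8 and 0.47, respectively". It plans for about 20% dropout, not split by arm.
- Background says of the neuropathy: "This condition often persists and may worsen even after treatment has ended, a phenomenon known as coasting". It also cites nearly 60% of patients with symptoms after the last chemotherapy session and 31% with the condition at 5 years.
- Table 1 schedules grading at nine visits from week 0 to week 60.
- Inclusion criteria (2.2) ask for "an expected survival of ≥6 months", and for chemotherapy completed at least 3 months earlier.

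**The concern.** A missing-data sensitivity analysis should show how far the conclusion depends on an assumption that the data cannot verify, here MAR. LOCF replaces MAR with another assumption, that a participant's grade never changes after the last visit attended. That would be a useful alternative if it were plausible or a deliberately conservative bound. Here it is neither. The protocol expects many participants in both groups to change grade, and the bias can run either way depending on who leaves and when.

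What is at stake is the robustness statement in the final report. The per-protocol analysis does not fill the gap, because it changes who is analysed and leaves the missing-data assumption as it was. The late visits matter most: the Discussion makes long-term effect a purpose of the trial, and carried-forward values accumulate there.

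**Working it through.** **The plan's own figure.** Inputs from 2.4: 0.8 and 0.47, two-sided alpha 0.05, power 80%, mean proportion 0.635.

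n = [1.96·√(2 × 0.635 × 0.365) + 0.8416·√(0.8 × 0.2 + 0.47 × 0.53)]² / 0.33² = (1.334 + 0.538)² / 0.1089 = 32.2, so 33 per group. With 20% dropout, 33/0.8 = 41.25, so 42 per group and 84 in total. Both figures reproduce; the sample size is not in dispute.

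**Inputs for the illustration.** From the documents: response 0.47 (read as standard care, since the order of the groups is not spelled out), response 0.80 (read as acupuncture), about 20% dropout overall, 42 per group. Assumed: dropout by arm, response status at the last visit attended, and, in case B, the fading of an early gain. The documents give none of these, so a range is shown.

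**Case A: improving course, no true difference.** True response is p = 0.47 in both arms. Dropouts leave before improving and are carried forward as non-responders. With dropout d, LOCF response is p(1 − d), so the spurious difference (acupuncture minus control) is 0.47 × (d_control − d_acupuncture). The last column is the chance of a significant result in favour of acupuncture from a pooled two-proportion z-test with 42 per arm (nominal 2.5%).

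| Dropout control / acupuncture | LOCF response control / acupuncture | Difference (points) | Chance of false benefit |
|---|---|---|---|
| 30% / 10% | 0.329 / 0.423 | +9.4 | 14.1% |
| 25% / 15% | 0.3525 / 0.3995 | +4.7 | 6.5% |
| 20% / 20% | 0.376 / 0.376 | 0 | 2.5% |
| 15% / 25% | 0.3995 / 0.3525 | −4.7 | 0.8% |
| 10% / 30% | 0.423 / 0.329 | −9.4 | 0.2% |

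Every row averages 20% dropout, as planned. If dropouts had already reached half of the final response, the 30%/10% row becomes 0.47 × (1 − 0.15) = 0.3995 against 0.47 × (1 − 0.05) = 0.4465, or +4.7 points (6.4%).

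**Case B: a gain that fades.** Acupuncture response is 0.80 at week 12 and 0.47 at week 60; control is 0.47 throughout. Equal 20% dropout occurs after week 12. LOCF at week 60 gives acupuncture 0.8 × 0.47 + 0.2 × 0.80 = 0.536 and control 0.47: +6.6 points, chance of false benefit 8.7%. No imbalance in dropout is needed.

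**Case C: a true effect.** With true response 0.80 and 0.47 (33 points) and dropouts carried as non-responders, equal 20% dropout gives 0.64 − 0.376 = 26.4 points. Dropout of 30% control and 10% acupuncture gives 0.72 − 0.329 = 39.1. Dropout of 10% control and 30% acupuncture gives 0.56 − 0.423 = 13.7. LOCF can therefore shrink a real benefit as well as create or inflate one.

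**The case against.** The best reply is that LOCF is only a sensitivity analysis, that the protocol's word for the list (including) leaves it open, and that an analysis plan not shown may add better methods. All of that stands in part. The primary analysis uses all randomised participants under MAR, so LOCF does not touch its estimate. It would also be wrong to infer that no other missing-data analysis is planned. But an open list does not make the method that is named, and fixed in advance, an informative one.

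Four stronger readings are tempting and are not supported:

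- *LOCF favours acupuncture.* Controls receive advice only and know their allocation, so they may leave more often. The acupuncture arm, however, carries 16 needling sessions, and the opposite split is also plausible. No section gives dropout by arm. If grades worsen over time, carrying forward early grades of departing controls flatters the control arm. The worsening described in Background therefore shows that grades move, not which arm gains. It is also weaker support than the expected response rates, because entry comes at least 3 months after chemotherapy.
- *LOCF gives false reassurance.* If the MAR analysis is unbiased and LOCF is not, the two would tend to disagree, which is a warning and not reassurance. Agreement would mislead only if the primary analysis were biased in the same direction, and nothing here shows that.
- *LOCF leaves MAR untested because it does not depart from it.* It does depart from MAR, but to an assumption the protocol contradicts.
- *The protocol will impute grades for participants who have died.* It does not say so. The survival criterion is an entry threshold, not a mortality forecast. The narrower point is that follow-up to week 60 outlasts that threshold, and the article sets no limit on carrying forward.

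**Conclusion.** The point holds in limited form. LOCF is the only missing-data sensitivity method named, and its no-change assumption conflicts with the protocol's expectation that 0.8 and 0.47 of the two groups improve by at least one grade. At the planned 20% overall dropout and with no true difference, the spurious effect in the splits examined ranges from −9.4 to +9.4 points under an improving course, and is 0 with equal dropout and the same course. It is +6.6 points with equal dropout if an early acupuncture gain fades.

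These figures rest on assumed dropout by arm, assumed status at the last visit, and response rates for which 2.4 names no visit. They show scale and are not a forecast. The harm is confined to the robustness claim: whether LOCF agrees or disagrees with the primary result, it says little about departures from MAR.

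**What to change.** In 4.2, replace LOCF with a delta-adjusted (tipping-point) multiple-imputation analysis of the neurotoxicity grade. Vary delta separately in each arm, so that worse-than-MAR and better-than-MAR outcomes among dropouts are examined on both sides, and report the combinations at which the conclusion changes. Add control-based imputation for acupuncture dropouts as a supporting analysis; alone it would not suffice, because it does not stress the control dropouts. State that grades are not imputed after death, and report deaths by arm.

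The cost is a text change and analysis programming, with no change to participants, visits or sample size. The resulting robustness statement may be less favourable. Make the change before outcome data are seen.

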### Statistical analysis sets

4.1

Full Analysis Set (Intention-to-Treat): All randomized participants will be included in the full analysis set and analyzed based on their initial randomized group assignment, irrespective of their compliance with the full intervention protocol. This set will constitute the primary population for the efficacy analysis.

Per-Protocol Set: This set will consist of participants who complete at least 80% of the planned treatment sessions (i.e., at least 13 sessions over the 12-week period) and have no major protocol deviations. It will be utilized for supportive sensitivity analyses.

Safety Analysis Set: This set shall encompass all participants who undergo at least one session of warm acupuncture and will be employed for the safety assessment of the intervention.

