### Statistical methods

4.2

Analysis of Baseline Characteristics: The baseline characteristics of each group will be delineated using appropriate summary statistics. For normally distributed continuous variables, the results will be shown as means ± standard deviations, with independent sample t-tests utilized for comparisons between groups. If the distribution is not normal, these variables will be reported as medians (interquartile ranges) and analyzed using the Mann–Whitney U test. Categorical data will be reported as frequencies (percentages) and analyzed for differences between groups using either the Chi-square test or Fisher’s exact test, depending on the situation.

Analysis of the Primary Outcome: The primary focus will be on the ordinal categorical variable representing the neurotoxicity grade according to NCI-CTCAE version 4.0. A Generalized Estimating Equations (GEE) approach or a mixed-effects ordinal logistic regression model will be utilized to analyse the primary outcome. This model will be used to conduct a statistical assessment comparing the effectiveness of warm acupuncture with alternative treatments, emphasizing differences between groups, temporal effects, and their interactions to determine its role in reducing neurotoxicity.

Analysis of the Secondary Outcomes: Secondary outcomes, which include the continuously measured scores from the EORTC QLQ-CIPN20 and the commonly used EORTC QLQ-C30 scales, will be analyzed using a linear mixed-effects model. This model will incorporate fixed effects for group, time, visit, and the interaction between group and time, while subject will be treated as a random effect. This approach aims to assess the variations in symptom burden and quality of life across groups and their changes over time.

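### The missing-data rule for the primary analysis names linear mixed models, which are not planned for the ordinal primary outcome, and it does not cover the permitted GEE option

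*Protocol article*

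**What the plan says.** All of this is in section 4 of the protocol article.

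- **Primary outcome and model (4.2).** "The primary focus will be on the ordinal categorical variable representing the neurotoxicity grade according to NCI-CTCAE version 4.0". Then: "A Generalized Estimating Equations (GEE) approach or a mixed-effects ordinal logistic regression model will be utilized to analyse the primary outcome".
- **Secondary outcomes (4.2).** The QLQ-CIPN20 and QLQ-C30 scores "will be analyzed using a linear mixed-effects model".
- **General missing-data rule (4.2, additional details).** "Missing data, assumed to be missing at random, will be managed using the likelihood-based estimation inherent to linear mixed models".
- **Rule for the primary analysis (same paragraph).** For participants who withdraw, "the primary efficacy analysis will follow the Intention-to-Treat (ITT) principle, with linear mixed models handling missing data under the Missing at Random assumption".
- **Robustness (same paragraph).** The text promises "sensitivity analyses, including the last observation carried forward method". No other method for missing data is named.
- **Population (4.1).** "All randomized participants will be included in the full analysis set and analyzed based on their initial randomized group assignment".

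**The concern.** The missing-data rule for the primary analysis belongs to a model that section 4.2 uses only for the secondary questionnaire scores. As written, an analyst cannot follow both statements for the primary outcome.

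The mismatch has substance because one of the two permitted primary models is GEE. GEE solves estimating equations and has no likelihood. In its standard unweighted form it generally needs data missing completely at random, or dropout that depends only on covariates in the model. The protocol assumes missing at random, which also allows dropout to depend on earlier observed grades. Inverse-probability weights or multiple imputation would bridge that gap, but neither is mentioned, and carrying the last observation forward does not bridge it.

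The setting makes this relevant. Section 2.4 expects about 20% dropout, Table 1 runs to week 60, section 2.7 leaves patients unblinded, and section 3.1 gives the control arm only advice. Dropout that follows persisting symptoms, and does so differently by arm, is plausible. The two permitted models also estimate different odds ratios, and the article gives no rule for choosing between them.

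**Working it through.** **1. The statements side by side.**

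| Outcome | Model in section 4.2 | Likelihood-based | Covered by the stated rule |
|---|---|---|---|
| Primary, first option | GEE | no | no |
| Primary, second option | mixed-effects ordinal logistic | yes | yes, once the word linear is corrected |
| Secondary scores | linear mixed model | yes | yes |

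This step needs no simulation. The steps below ask only how much it could matter.

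**2. The plan's own figures.** Section 2.4 gives response rates of 0.80 and 0.47, two-sided alpha 0.05 and power 80%. The pooled two-proportion formula gives 33 per group, as stated. With 20% dropout, 33/(1 − 0.20) = 41.25, so 42 per group and 84 in total. These figures reproduce and are not in dispute.

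**3. A scenario with no true effect (all parameters assumed).** The inputs are 60,000 subjects, a four-level grade, a random-intercept SD of 2 on the logit scale and the same improvement in both arms. The dropout hazard per visit after a grade of 2 or more is 0.08 in control and 0.02 in acupuncture. Dropout by week 60 is 26% and 8%, about 17% overall.

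- True P(grade ≥2) at week 60 is 0.327 control and 0.322 acupuncture. Log odds ratio: ln(0.322/0.678) − ln(0.327/0.673) = −0.023.
- Observed cases give 0.281 and 0.314. Log odds ratio: ln(0.314/0.686) − ln(0.281/0.719) = 0.158.
- Bias: 0.158 − (−0.023) = 0.18, and exp(0.18) is about 1.2. At week 12 the spurious odds ratio is about 1.07.

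Observed cases are what GEE with independence working correlation uses at each visit. Control patients with high grades leave, so control looks better and the bias runs against acupuncture.

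**4. Sensitivity of that scenario.** Comparable simulations with the outcome reduced to grade ≥2 gave these week-60 odds ratios, where the truth is 1.0:

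| Setting | Odds ratio |
|---|---|
| Independence, hazards 0.08 and 0.02 | 1.17 to 1.22 |
| Exchangeable working correlation, arm-differential dropout | 0.96 to 0.98 |
| Equal dropout mechanisms in both arms | 1.00 to 1.03 |

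**5. A scenario with a true effect (all parameters assumed).** An ordinal grade was simulated for 400,000 subjects per arm, with 16% to 20% dropout per arm depending on the previous grade as shown. The true marginal log odds ratio is −0.620 (odds ratio 0.54). The unweighted observed-case cumulative-logit fit gave:

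| Dropout mechanism | Log OR | OR | Share of effect lost |
|---|---|---|---|
| Same in both arms | −0.617 | 0.54 | under 1% |
| Depends on grade in control only | −0.478 | 0.62 | 1 − 0.478/0.620 = 23% |
| Opposite directions by arm | −0.365 | 0.69 | 1 − 0.365/0.620 = 41% |

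**6. Scale against sampling error.** With 42 per arm and the dropout of step 3, about 42 × 0.74 = 31.1 control and 42 × 0.92 = 38.6 acupuncture patients are observed at week 60. The standard error of the log odds ratio for grade ≥2 is √[1/(31.1 × 0.281 × 0.719) + 1/(38.6 × 0.314 × 0.686)] = 0.53. The bias of 0.18 is about a third of that.

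**7. Different odds ratios.** With an assumed random-intercept SD of 2, the attenuation factor is 1/√(1 + 0.346 × 4) = 0.648. A subject-specific odds ratio of 3.0 then corresponds to a population-average one of exp(0.648 × ln 3) = 2.04.

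**The case against.** The strongest reply is that linear is a slip for mixed models in general. On that reading the mixed-effects ordinal logistic option already satisfies the stated principle. This stands: a reader might infer that the missing-data method exists nowhere in the primary analysis, and that would be too strong. The reading does not rescue the GEE option.

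A second reply is that the bias depends on assumptions absent from the article. No working correlation is named, and section 2.4 gives one overall dropout rate with no split by arm. This also stands. A reader might infer that GEE will give a biased result, or a false claim of benefit. The documents support only that it may be biased, and in the null scenario of step 3 the bias works against acupuncture. An exchangeable structure reduces the bias there but does not in general guarantee validity under missing at random.

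A third reply is that a condensed article may leave the choice between GEE and a mixed model to an analysis plan. For the choice alone, that is fair. The missing-data rule, however, is stated here and presented as predefined, and it does not fit. That is an inconsistency, not an omission. The gap between odds ratios of 3.0 and 2.0 is a difference of estimand under an assumed SD, not an error in either model.

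**Conclusion.** The point holds in this limited form and should be fixed. Section 4.2 assigns the primary analysis a missing-data method from a model planned only for secondary scores. One permitted primary model, the ordinal mixed model, fits the likelihood and missing-at-random principle if correctly specified. The other, unweighted GEE, does not in general.

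The inconsistency rests on the text alone. The size of any bias rests on assumed dropout. On the log-odds scale it ranged from close to zero up to about 0.18 in the null scenario (about a third of a standard error at this sample size), and up to 0.620 − 0.365 = 0.255 where a true effect was assumed. It needs dropout that depends on earlier grades differently by arm, and these figures use an independence working correlation. The sample size is unaffected.

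The documents do not support ruling out GEE as the primary analysis. With suitable weights or after multiple imputation it would be an equally valid choice, and a population-average odds ratio is a legitimate target.

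**What to change.** - **Primary model (4.2).** Name one model before outcome data are seen. Preferably this is a mixed-effects cumulative-logit model fitted by maximum likelihood, with group, categorical visit, group-by-visit, the planned prognostic covariates and a subject random intercept. Say whether baseline is a covariate or a modelled visit, because section 2.2 restricts baseline to grade 2 or more and this strains a proportional-odds fit that includes it.
- **Missing data (4.2, additional details).** For the primary outcome, replace the reference to linear mixed models with the likelihood of that ordinal model under missing at random. Keep the linear mixed model wording for the questionnaire scores.
- **If a population-average odds ratio is wanted.** Use GEE only with inverse-probability-of-dropout weights or after multiple imputation, as the primary or as a sensitivity analysis, and say which.

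The cost is about two sentences, with no new data and no change in sample size. The downside is that the mixed model reports a subject-specific effect, while weighted or imputed GEE needs some extra analysis work.
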